## Abstract

**Introduction:**

The prevalence of gestational diabetes mellitus (GDM) is rising in the UK and is associated with maternal and neonatal complications. National Institute for Health and Care Excellence guidance advises first-line management with healthy eating and physical activity which is only moderately effective for achieving glycaemic targets. Approximately 30% of women require medication with metformin and/or insulin. There is currently no strong evidence base for any particular dietary regimen to improve outcomes in GDM. Intermittent low-energy diets (ILEDs) are associated with improved glycaemic control and reduced insulin resistance in type 2 diabetes and could be a viable option in the management of GDM. This study aims to test the safety, feasibility and acceptability of an ILED intervention among women with GDM compared with best National Health Service (NHS) care.

**Method and analysis:**

We aim to recruit 48 women with GDM diagnosed between 24 and 30 weeks gestation from antenatal clinics at Wythenshawe and St Mary’s hospitals, Manchester Foundation Trust, over 13 months starting in November 2022. Participants will be randomised (1:1) to ILED (2 low-energy diet days/week of 1000 kcal and 5 days/week of the best NHS care healthy diet and physical activity advice) or best NHS care 7 days/week until delivery of their baby. Primary outcomes include uptake and retention of participants to the trial and adherence to both dietary interventions. Safety outcomes will include birth weight, gestational age at delivery, neonatal hypoglycaemic episodes requiring intervention, neonatal hyperbilirubinaemia, admission to special care baby unit or neonatal intensive care unit, stillbirths, the percentage of women with hypoglycaemic episodes requiring third-party assistance, and significant maternal ketonaemia (defined as ≥1.0 mmol/L). Secondary outcomes will assess the fidelity of delivery of the interventions, and qualitative analysis of participant and healthcare professionals’ experiences of the diet. Exploratory outcomes include the number of women requiring metformin and/or insulin.

**Ethics and dissemination:**

Ethical approval has been granted by the Cambridge East Research Ethics Committee (22/EE/0119). Findings will be disseminated via publication in peer-reviewed journals, conference presentations and shared with diabetes charitable bodies and organisations in the UK, such as Diabetes UK and the Association of British Clinical Diabetologists.

**Trial registration number:**

NCT05344066.

STRENGTHS AND LIMITATIONS OF THIS STUDYThis mixed-method feasibility study includes both quantitative and qualitative evaluation of the acceptability of the dietary intervention.This study has been informed by an experienced patient and public involvement and engagement group.This study involves a small sample size and is not powered to show efficacy of the intervention.Women joining this study are likely to be highly motivated and adherence may not reflect that seen in the wider general population.

## Introduction

### Background

In the UK up to 16% of pregnant women develop gestational diabetes mellitus (GDM) and the incidence is rising, in part due to increasing rates of obesity and maternal age.^1 2^ GDM is associated with maternal and neonatal complications (the risk increases with poor glycaemic control), including macrosomia, shoulder dystocia, caesarean sections, neonatal hypoglycaemia and/or hyperbilirubinaemia, preterm delivery, pre-eclampsia and stillbirth.^2^ Women who have had GDM have an estimated 7-fold to 10-fold risk of developing type 2 diabetes (T2DM) later in life, and their children have a higher risk of developing adult obesity and T2DM.^2–4^

Excessive weight gain in pregnancy is a particular problem for women with GDM.^5^ Harper *et al* demonstrated that, in women with GDM, every additional 1 lb/week gained following diagnosis of GDM resulted in a 36%–83% increased risk of pre-eclampsia, caesarean section, macrosomia and large for gestational age babies.^5^ Such studies highlight the importance of adequate weight control throughout pregnancy in women with GDM in order to reduce both maternal and neonatal complications.

First-line therapy for GDM is diet and physical activity. National Institute for Health and Care Excellence (NICE) guidance encourages a healthy diet with increased fruit and vegetables, low-glycaemic index (GI) foods, reduced refined sugars, regular mealtimes and regular physical activity.^6 7^ These dietary measures fail to achieve glycaemic targets in ~30% of women who require medication with metformin and/or insulin.^8^ A range of dietary approaches have been studied including daily diets promoting low-GI diets (limiting refined and promoting complex carbohydrates), continuous modest energy restriction (1800 kcal/day) and low carbohydrate diets.^9^ There is currently no strong evidence base for any particular dietary regimen to improve outcomes in GDM.

### Intermittent low-energy diets (ILED)

The pathogenesis of GDM is strongly linked to obesity and chronic insulin resistance with many clinicians viewing GDM as a form of evolving T2DM. ILEDs typically include several days of a food based or meal replacement (eg, drinks/bars) low-energy diet (650–1000 kcal), with a standard healthy (non-restrictive) diet recommended on the remaining days of the week. These diets are associated with significant reductions in weight, insulin resistance and hyperglycaemia in patients with pre-diabetes (Haemoglobin A1C (HbA1c) between 42 and 47 mmol/mol, impaired glucose tolerance, or impaired fasting glycaemia), those with T2DM, and otherwise healthy subjects with overweight/obesity.^10–17^ These changes are equivalent to, or greater than, those achieved with standard daily energy restriction. A popular intermittent diet involves 2 consecutive or non-consecutive days/week of a low-energy diet (650–1000 kcal) and 5 days of normal eating/week, known as the 5:2 diet. The Manchester Intermittent versus Daily Diabetes App Study (MIDDAS), a study comparing an ILED and a continuous low-energy diet in T2D conducted in our unit, has shown the feasibility and safety of an ILED (800 kcal for 2 days/week) in patients with T2DM and obesity, including those using insulin.^18^ At the end of the study, approximately 70% of participants in the ILED group completed the study and achieved a 6% reduction in their baseline body weight. 42% achieved an HbA1c of <48 mmol/mol.^18^ Given the strong overlap between GDM and T2DM, an ILED may be a promising dietary intervention for those with GDM.

A successful dietary approach to glycaemic control could empower women to take charge of the management of their GDM. Women with GDM are motivated to modify their diet driven by a desire to improve foetal outcomes.^19–21^

Our patient and public involvement and engagement (PPIE) work indicates that women find the current NICE healthy eating guidance^6 7^ confusing and vague. Our PPIE work has indicated that women are keen to try alternative dietary approaches, particularly if alternative diets are more effective in preventing the need to progress to medications such as metformin and insulin.

### Aim

The aim of this trial is to test the safety, feasibility and acceptability of an ILED in GDM to inform a future large-scale randomised controlled trial (RCT).

## Methods

### Trial design

The study is a 28-week feasibility two-arm RCT in one National Health Service (NHS) trust performed in patients with GDM and body mass index (BMI) ≥27.5 kg/m^2^, or ≥25 kg/m^2^ in high-risk minority ethnic groups (ie, South Asian, Black African and African Caribbean) in Greater Manchester between December 2022 and July 2024.^22 23^ There will be an embedded qualitative substudy for participants and healthcare professionals (HCPs). Due to the nature of the intervention, it will not be possible to blind the participants, clinicians or study team to the treatment allocation after randomisation (the statistician and laboratory technicians will remain blinded).

### Trial setting and recruitment

Participants will be recruited from antenatal clinics at Wythenshawe and St Mary’s Hospitals, Manchester Foundation Trust (MFT) between November 2022 and December 2023. This is an urban area within Greater Manchester, and MFT serves patients from a wide range of minority ethnic and sociodemographic backgrounds. Women may self-refer to the antenatal clinic or be referred by their primary care team. Assessments will be carried out at MFT, or remotely if required by COVID-19 restrictions. The qualitative substudy will be carried out at MFT, remotely, or at a location of the participant’s choosing. We aim to recruit eligible participants over a period of 13 months. Potential participants will be given written information about the study and the opportunity to ask questions about the study prior to providing written consent (online supplemental files 1 and 2).

10.1136/bmjopen-2023-078264.supp1Supplementary data

10.1136/bmjopen-2023-078264.supp2Supplementary data

### Eligibility criteria

#### Participant flow

Participants who fulfil the broad eligibility criteria will be notified about the trial by the GDM nurse/midwife at the time of their diagnosis. Those who are interested will be provided with a comprehensive patient information sheet (online supplemental file 1) and more detailed eligibility screening questions (figure 1). They will be asked to attend their first appointment having fasted for at least 6 hours and complete a 4-day food diary (in line with our department’s usual care). On attending their first routine clinic appointment, interested participants will receive further information from the research team. They will have the opportunity to ask questions, have their eligibility confirmed and will be asked for their written consent to take part. Baseline assessments will be taken and participants will be randomised to their allocated treatment group using an online randomisation platform. Participant flow through the study is demonstrated in figure 2.

**Figure 1 F1:**
[figure not shown]
Inclusion and exclusion criteria. BMI, body mass index; GDM, gestational diabetes; NHS, National Health Service; OGTT, oral glucose tolerance tests.

**Figure 2 F2:**
[figure not shown]
Participant flow through trial. GDM, gestational diabetes; NHS, National Health Service

#### Sample size

We plan to recruit 24 participants per study arm (n=48) which, when considering an estimated attrition rate of 15%, will provide complete outcome data on 40 participants.^24–26^ It has been estimated that 24 participants per group will be sufficient to determine study outcomes, in line with sample size recommendations for feasibility studies.^27–29^

This number will allow us to enable estimation of recruitment/retention parameters with sufficient precision. For example, based on 40 completed participants, it will enable recruitment rates in the region of 25% to be estimated with an error of ±13.42% at most; retention of 85% will be estimated with error of ±11.07% at most. It is also sufficient for estimation of variability (eg, SD) in gestational weight gain and capillary glucose concentrations (proposed outcomes for the future definitive trial) with negligible bias.^30^

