### Outcomes

#### Primary outcomes

Uptake rate measured as a percentage of eligible participants who consent to take part, including the proportion of women who were screened who did not meet the eligibility criteria, and the number of women who did not give consent to take part.Recruitment rate measured as the number of eligible participants who consent to take part per month.Retention rate measured as the number of randomised participants who complete the trial (those who attend the final visit) and the percentage of participants who attend all eight visits.Adherence to the dietary interventions assessed from self-reported adherence to the potential low-calorie days between randomisation and delivery.Completion of self-assessed glucose and ketone readings assessed as a percentage of the required readings.Safety outcomes:Percentage of women following ILED/best NHS care with hypoglycaemia (episodes of blood glucose of <3.0 mmol/mol) and hypoglycaemia requiring third-party assistance as measured by participants.Percentage of women who develop significant ketonaemia in both groups (defined as ≥1.0 mmol/L) as measured by participants.Percentage of neonatal hypoglycaemic episodes requiring intervention (blood glucose checked 2 hours post delivery and 2 hours thereafter for 12 hours according to local protocol), neonatal birth weight, gestational age at delivery, hyperbilirubinaemia/jaundice and/or admission to Special Care Baby Unit or neonatal intensive care, and stillbirths.The incidence and rate of other adverse events (eg, headaches, lethargy, constipation or complications requiring hospital admission) between the start of the trial intervention and delivery recorded as mild, moderate and severe, as defined by Common Terminology Criteria for Adverse Events (CTCAE V.5).^34^ Hospital admission for routine labour and delivery will not be classified as an adverse event.

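### The two precision figures in the sample size section use 40 completers as denominator, which fits neither uptake (eligible women) nor retention (randomised women); both errors are conservative

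*Protocol article*

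**What the plan says.** The Sample size section sets a target of 24 women per arm, 48 in all. It adds that this number, "when considering an estimated attrition rate of 15%, will provide complete outcome data on 40 participants". Precision is then illustrated on those completers. The sentence on recruitment reads: "it will enable recruitment rates in the region of 25% to be estimated with an error of ±13.42% at most". The one on retention reads: "retention of 85% will be estimated with error of ±11.07% at most". No confidence level is given.

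The Primary outcomes section defines the quantities concerned:

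- Uptake: "Uptake rate measured as a percentage of eligible participants who consent to take part". The denominator is eligible women.
- Recruitment rate: a number of consenting women per month. It is a count over time, and Table 1 (Progression criterion) uses it in that form.
- Retention: "Retention rate measured as the number of randomised participants who complete the trial". The denominator is the women randomised.

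**The concern.** A proportion's precision depends on its denominator, and completers are the denominator of neither quantity. Among completers, retention is 100% by construction, so its uncertainty cannot be worked out on that group. A recruitment proportion of 25% must count the women who declined, and none of them can be among the completers.

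The label adds to the difficulty. A recruitment rate of 25% does not fit the article's own definition, which is a monthly count. The only defined outcome that it can be is uptake. That is an interpretation, but no other proportion in the outcome list fits.

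Uptake and retention are both primary outcomes and progression criteria. A reader who relies on this paragraph gets a wrong account of how precisely the trial will estimate them, and the uptake figure is wrong by a wide margin.

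**Working it through.** **Inputs.** From Sample size: 48 randomised, 15% attrition, 40 completers, rates of 25% and 85%, stated errors of 13.42% and 11.07%. From Primary outcomes: the denominators. Assumed: a two-sided 95% level (z = 1.96), which the first step bears out.

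**Formula.** Half-width h = 1.96 × √(p(1 − p)/n).

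**1. Reproduce the stated figures (n = 40).**

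- p = 0.25: 1.96 × √(0.1875/40) = 13.42%. Matches.
- p = 0.85: 1.96 × √(0.1275/40) = 11.07%. Matches.

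Solving the formula for n from the stated errors gives 39.99 and 39.97. Alternatives do not match both figures:

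| Method | 25% | 85% |
|---|---|---|
| n = 48 | 12.25% | 10.10% |
| n = 24 (one arm) | 17.32% | 14.29% |
| n = 40, Wilson | 13.00% | 11.01% |
| n = 40, continuity correction | 14.67% | 12.32% |

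The attrition step is sound: 48 × 0.85 = 40.8.

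**2. Retention on the 48 randomised.**

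- p = 0.85: 1.96 × √(0.1275/48) = 10.10%, against 11.07% stated, a gap of 0.97 points.
- Exact (Clopper-Pearson) 95% interval for 41/48: 72.2% to 93.9%.

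**3. Uptake on eligible women.** The document gives no number of eligible women. Assume that 48 women consent and all are randomised, so that eligible = 48/uptake.

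| Uptake | Eligible (assumed) | Half-width |
|---|---|---|
| 25% | 48/0.25 = 192 | 1.96 × √(0.1875/192) = 6.12% |
| 15% | 48/0.15 = 320 | 1.96 × √(0.1275/320) = 3.91% |
| 10% | 48/0.10 = 480 | 1.96 × √(0.09/480) = 2.68% |

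At 25% the stated error is 13.42/6.12 = 2.2 times too large. If only 40 were recruited at 25%, the eligible number would be 160 and the half-width 6.71%, so the conclusion does not hinge on reaching 48.

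**4. The wording *at most*.** With n fixed, the half-width grows as the rate moves towards 50%. For retention with n = 48:

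- 80%: 1.96 × √(0.16/48) = 11.3%.
- 70%: 1.96 × √(0.21/48) = 13.0%.

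At the quoted 85%, the correct 10.1% lies below the stated 11.07%. For uptake, a nearby rate stays well below the stated 13.42%: at 30%, 48/0.30 = 160 eligible and 1.96 × √(0.21/160) = 7.1%.

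**The case against.** The strongest reply is that nothing in the trial depends on these two figures. At the quoted rates both overstate the error, so the plan promises less precision than it will have. No outcome, analysis or progression rule uses them. The section offers them as an example, after resting 24 per group on published feasibility recommendations, and it also appeals to the estimation of standard deviations. All of this stands, and it makes the point minor. It does not make the figures right: the stated denominator contradicts the outcome definitions in the same article, and an unseen analysis plan cannot resolve that.

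Several stronger readings are tempting, and the document does not support them:

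- *The sample size loses its justification.* It does not. Correcting the denominators improves the precision at the quoted rates, and the figures are not the only basis given for 48.
- *The plan misjudges which progression criteria it can decide.* A reader might apply n = 40 at the 15% uptake cut-off, get about ±11%, and see an interval reaching from red to green. The article states no precision at 15%, and Table 1 is not tied to any interval-based rule. A value sitting on a cut-off straddles it at any n: even ±3.9% around 15% covers amber and green.
- *The claim of a maximum is false.* At exactly 25% and 85% it is not breached. The 70% retention example changes the quoted rate. The wording is loose, because each figure is the half-width at one rate and not a worst case.
- *The normal approximation is unfit near 85%.* At n = 48 the Wilson half-width is 10.06%, against 10.10%. The difference is immaterial.

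**Conclusion.** The point holds as a minor error of denominator and label. Both stated figures are computed on 40 completers, whereas the article's own definitions call for eligible women (uptake) and randomised women (retention). For uptake the discrepancy is material: ±13.42% stated, against about ±6.1%. For retention it is small: ±11.07% stated, against ±10.1%. Both errors are conservative, and the sample size of 48 stands.

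The retention figure needs only the planned 48 and the 95% level. The uptake figure rests on two further assumptions: that the 25% means uptake, and that the number of eligible women can be back-calculated from full recruitment at that rate.

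**What to change.** Reword the precision paragraph in Sample size as follows:

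- Call the 25% proportion uptake, and keep recruitment rate for the monthly count.
- Base its precision on the expected number of eligible women, labelled as an assumption: if 48 are recruited at 25% uptake, about 192 eligible and ±6.1%; at 15% uptake, about 320 eligible and ±3.9%.
- Base retention on the 48 randomised: 85% is estimated to ±10.1% (exact 95% interval for 41/48, about 72% to 94%).
- Replace *at most* with a statement that each half-width applies at the quoted rate and that retention nearer 50% is estimated less precisely, for example ±13.0% at 70%.
- State the 95% level.

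The cost is one paragraph of text. Sample size, conduct, outcomes and progression criteria do not change.

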#### Randomisation

The randomisation schedule will be independently set up and known only by the trial statistician. The trial statistician will be blinded to the participant’s identity using ‘sealed envelope’ software (https://www.sealedenvelope.com/). Randomisation will be carried out by generating an online pseudorandom list with random permuted blocks of varying size, known only to the statistician, and will be stratified for two variables:

Age (18–35, >35 years).BMI (27.5–34.99 kg/m^2^ and>35 kg/m^2^; >25–32.49 kg/m^2^ and >32.5 kg/m^2^ for high-risk minority ethnic groups (ie, South Asian, Black African and African Caribbean).

These stratification variables have been chosen to reduce potential bias as we expect varying severity of GDM with increasing age and BMI and possible differences in diet adherence.^31^

Treatment to intervention and control groups will be allocated in a 1:1 ratio. A member of the research team who will be unaware of the randomisation algorithm (principal investigator, clinical research nurse, clinical research fellow or project manager) will trigger the randomisation procedure onsite; participants and clinicians will then be informed of the allocated treatment group. Clinicians will not be blinded due to the need to remain astute to safety, adherence and side effects, requiring open and honest discussions with patients at each appointment. The statistician will remain blinded to treatment allocation until all outcome measures for all subjects have been collected.

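### The statistician is described both as the only person who knows the randomisation schedule and as blinded to allocation; masking participant identity does not reconcile the two.

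*Protocol article*

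**What the plan says.** The Randomisation section of the protocol article makes four statements about the statistician:

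- On the schedule: "The randomisation schedule will be independently set up and known only by the trial statistician".
- On the method: randomisation works by "generating an online pseudorandom list with random permuted blocks of varying size, known only to the statistician".
- On the safeguard: "The trial statistician will be blinded to the participant’s identity using ‘sealed envelope’ software".
- On blinding: "The statistician will remain blinded to treatment allocation until all outcome measures for all subjects have been collected".

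The Trial design section explains that participants, clinicians and the study team cannot be blinded once a woman is randomised, and adds in brackets that "the statistician and laboratory technicians will remain blinded".

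The person who triggers the allocation on site is someone else: "A member of the research team who will be unaware of the randomisation algorithm". The article mentions no second statistician, does not say that the arms on the list are coded, and does not say when the statistician first receives participant records.

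**The concern.** A randomisation schedule is the ordered list of arm assignments. The article gives sole knowledge of that list to the person it then describes as not knowing the assignments. Both are positive statements in the current text, so this is a conflict and not a detail left to the SAP or the full protocol.

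In an open-label trial, blinding of the statistician and of the laboratory is all the blinding that is claimed, and a reader of the results will give it weight. The Statistical methods section plans summaries by group and of the group difference, and considers a per-protocol analysis as secondary. The safety outcomes are reported for both arms. If the analyst can tell the arms apart while these analyses are being specified and derived, the protection that the article advertises is missing at that step.

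**Working it through.** The article gives no figure on this point, so the check sets its statements side by side.

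**1. What the list holder knows.** The ratio is fixed: "Treatment to intervention and control groups will be allocated in a 1:1 ratio". The list uses permuted blocks stratified by age and BMI. Whoever knows it can read off the arm for any given stratum and position.

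**2. Two readings of the sentence on the list.** In the sentence on permuted blocks, the words about what only the statistician knows could refer to the list or just to the block sizes. The reading does not matter here, because the section's opening sentence already gives the statistician the whole schedule.

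**3. What masking identity achieves.** It keeps names from the statistician. An analyst works with records that carry a study number and baseline data, and needs no names. A record can be tied to a slot on the list by its randomisation number, if the record carries one. Otherwise its stratum and order of entry could serve.

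**4. How hard the second route would be.** The planned size is small: "We plan to recruit 24 participants per study arm (n=48", so 2 × 24 = 48.

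| Assumption about the BMI bands | Strata | Average women per stratum |
|---|---|---|
| Lower and upper band, with cut-offs that depend on ethnic group | 2 age × 2 BMI = 4 | 48 / 4 = 12 |
| The four printed BMI bands kept apart | 2 age × 4 BMI = 8 | 48 / 8 = 6 |

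With about 6 to 12 women per stratum, matching by order of entry is straightforward for someone who has the list, age, BMI, ethnic group and randomisation dates. That the statistician would have these before outcome collection ends is an assumption; the article does not say.

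**5. What would make the statements compatible.** Any one of three arrangements could do so:

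- different people hold the list and do the analysis;
- the arms on the list are coded and the code is kept from the statistician;
- the statistician receives no linkable records until outcome collection is complete.

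The article states none of these. The safeguard that it does state is a different one and does not do the same work.

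**The case against.** The best defence is that knowing a schedule is not the same as knowing which outcome record filled which slot. If no linkable data reach the statistician until outcomes are complete, the sentences can be reconciled. That is fair. It means one cannot conclude that blinding was absent in practice, or that all 48 allocations were known against records. A reader might infer either, but the article does not say what data the statistician receives or when. The defence still depends on an arrangement that the article does not describe.

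A reader might also infer that the statistician creates the list. The text says only that it is set up independently. Sole knowledge of it is explicit, and that is enough for the point.

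The case that little depends on analyst blinding here is largely right:

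- The analysis is descriptive, without significance tests. The main analysis is by intention to treat, and no imputation is used.
- Uptake and recruitment are counted at consent, before allocation.
- Hypoglycaemia (below 3.0) and ketonaemia (1.0 mmol/L or above) have fixed thresholds, adverse events are graded by CTCAE, and Table 1 fixes the progression criteria.
- The adherence criterion concerns the ILED arm only, so deriving it requires knowing the arm.
- Ketones are measured on two random days a week in one arm, and on and the morning after the low-energy days in the other. The data pattern could reveal the arm to an analyst who never saw the list.

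Nor can it be said that the SAP comes too late. The article promises it before trial analysis, it is not shown here, and per-protocol rules are commonly left to it.

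**Conclusion.** The claim of statistician blinding is contradicted as written, and the stated masking of identity does not rescue it. This conclusion rests on reading one person into the references to the statistician in the two sections, and on the ordinary meaning of a randomisation schedule as the list of assignments.

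The size is modest. A stated design property is unsupported, in a feasibility trial that makes no inferential comparison. No bias in any estimate is shown or claimed. It would also be wrong to infer that allocation concealment is compromised: the person triggering randomisation does not know the algorithm, and nothing in the article suggests that upcoming assignments reach those who enrol. The text should still be corrected, because published results would otherwise repeat a blinding claim that the trial's own description undercuts.

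**What to change.** If the arrangement can still be changed:

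- Have the list generated and held by the online randomisation service already in use, or by a person with no role in the analysis. The trial statistician specifies only the strata, the ratio and the block-size range.
- Release data to the analysing statistician with coded arms only, until outcome collection is complete and the SAP is final.
- Acknowledge that ketone schedules and ILED adherence may still reveal the arm. Blinding would then be described as partial for those data.

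If the statistician already holds the list, remove the statistician-blinding statements from the Trial design and Randomisation sections, and state that the statistician had access to the allocation list.

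The cost is a change in who can see the list and a few sentences of text, or the text alone in the second case. The article does not describe the service's access settings. If the service cannot keep the list from the statistician, a person outside the analysis has to hold it. Sample size, outcomes and planned summaries are unaffected.
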